### Procedure

Eligible persons for the study were drawn from official registers of all persons over 80 years of age in the two municipalities. Equal numbers from the two municipalities were listed in random order. The persons were included in the sample consecutively using the simple random sampling chart until the intended sample size was reached. Invitation letters were then sent to all persons in the sample (n = 2031) asking them to participate in the study. The letter described the study, how it would be conducted and what would be expected of those consenting to participate. The letter stressed the fact that participation was voluntary. The letter was followed up by a telephone call about 1-2 weeks later. 365 persons out of 2031 persons were either non-eligible (n = 147) or not traceable (n = 218). The remaining persons (n = 1666) was then informed verbally about the study and given the opportunity to ask questions if anything was unclear. They were also asked personally if they would like to participate, while again stressing that this was voluntary. 1120 persons out of the 1666 persons were unwilling or unable to participate (no interest n = 936, lack of time n = 116, not having the strength n = 68). For the 546 persons who consented to participate, a time for the first visit, when they also would have to hand in their written consent, was decided.

After a baseline interview, 491 persons were found to fulfil the study criteria and were randomised to one of the three study arms by the use of sealed opaque envelopes. If eligible persons lived together, they were always allocated to the same intervention group.

One hundred and fourteen persons were allocated to the control group, 178 to the preventive home visits and 199 to the senior meetings. Four persons allocated to preventive home visit and 23 to the senior meetings withdrew their consent because they did not want to participate in the allocated intervention. Further, 5 persons participating in senior meetings fell ill. Thus, 459 persons were included in the study, 114 in the control group, 174 in the preventive home visits and 171 in the senior meetings.

The study was preceded by a pilot study with the purpose of testing intervention, inclusion criteria and logistics in which the elderly themselves, the professionals and the research assistants were involved. The research assistants were occupational therapists, physiotherapists or nurses. They were trained and inter-rater reliability was tested. To enhance the quality of outcome measurements, study protocol meetings were held throughout the study. Further, another research assistant who had not conducted the interview was responsible for the data entry at baseline. These data was verified in a second step by yet another of the research assistants. Data entry at follow-ups was in charge of the interviewers. These data were verified in a second step by another research assistant who had not conducted the interview.

All participants received a first visit that comprised an interview, assessment and observation. The first visit, i.e. the baseline interview, was performed in the participant's home by research assistants well trained in interviewing, assessing and observing according to the guidelines for the different outcome measurements. Follow-up data were also collected in the participant's home by well-trained research assistants. The research assistants that assessed the outcomes were not involved in the intervention and were blind to group assignment.

Follow-up data were collected in all groups at 3 months, 1 year and 2 years after intervention (see figure 1).

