### Statistical analysis and power calculations

The calculations will be based on the expected relative change in time, i.e. we assume that the intervention group "Senior meetings and a follow-up home visit" will change slightly or not at all in functional status; that the intervention group "Preventive home visit" will change by 15% in relation to the intervention group with Senior meetings while the "Control group" will deteriorate 20% more than the intervention group "Preventive home visit". Power calculation ensures that, if the hypotheses are true, we will be able to discover a difference of at least 15% between the intervention groups and a difference of at least 20% between the intervention groups and the control group.

Since a level of significance of alpha = 0.05 and a power of 80% are required to compare the intervention groups in a two-sided test, at least 112 persons will be required in each intervention group to be able to observe a difference of at least 15% between the groups. A comparison between the control group and the intervention groups will require 72 persons in the control group, if we assume a difference of at least 20%. A total of about 300 persons will be required.

However, to allow for drop-outs, it was estimated that a total of about 450 persons would need to be included in the study.

The analyses will be made on the basis of the intention-to-treat principle, which means that the participants will be analysed on the basis of the group to which they have been randomised [34]. Both descriptive and analytical statistics will be used to compare the groups as well as for analyses measuring changes over time. Non-parametric statistics will be used in all cases where ordinal data are analysed. Otherwise parametric statistics will be used.

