Although few drop outs are desirable, it is important to ask whether those who participated in the study are representative of the population of interest. In our study, the baseline characteristics indicated that about 80% of the participants experienced good/very good or excellent health. Nevertheless, the frailty indicators reveal that the participants experienced different degrees of frailty. Approximately 40% of the participants experienced fatigue, 60% were visually impaired, and 22-36% reported a low level of physical activity. This can be seen as evidence for the capture of the target group. However, according to statistical theories, proper randomisation should guarantee that the groups are comparable in baseline characteristics and ensure that differences between groups are due to trial effects [34]. In this study there were no statistically significant differences between the control group and the interventions groups in baseline characteristics in terms of demographic and frailty indicators, showing that randomisation was properly performed.

To enhance its quality, the study was preceded by a pilot study with the purpose of testing intervention, inclusion criteria and logistics by involving pensioners' representatives and responsible professionals in the municipality in the different phases of the planning. Meetings were held with pensioners' representatives to discuss the content and the extent of the interview. Pilot interviews were conducted in order to test the questions and the outcome measurements. Their experiences of the interview were discussed in the groups, which led to a clarification of questions and removal or substitution of outcome measurements.

Discussions were also held with the representatives about the content of the interventions and the educational material used in the interventions. The fact that the elderly themselves were involved in planning and developing the programme in close cooperation with the professionals should ensure that it will meet their needs [40]. This might mean that the intervention itself is more likely to be effective.

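### Intention-to-treat is promised, but the study population is set at 459 after 32 of the 491 randomised persons, 28 of them from senior meetings, are taken out after allocation

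*Protocol article*

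**What the plan says.** The Procedure section of the protocol article reports that, after the baseline interview, "491 persons were found to fulfil the study criteria and were randomised to one of the three study arms". It gives the arms as follows: "One hundred and fourteen persons were allocated to the control group, 178 to the preventive home visits and 199 to the senior meetings".

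Two kinds of loss after allocation follow. The first is refusal of the arm drawn: "Four persons allocated to preventive home visit and 23 to the senior meetings withdrew their consent because they did not want to participate". The second is illness: "Further, 5 persons participating in senior meetings fell ill". The section then closes the count: "Thus, 459 persons were included in the study, 114 in the control group, 174 in the preventive home visits". Senior meetings are left with 171.

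The section on statistical analysis and power calculations states the intention-to-treat principle, under which "participants will be analysed on the basis of the group to which they have been randomised".

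Two other places bear on which population is meant. Table 2 (baseline characteristics) is headed 114, 174 and 171, which is the 459. The time plan, by contrast, gives 491 as the number whose inclusion was completed in November 2008. The Discussion then takes the absence of significant baseline differences as "showing that randomisation was properly performed".

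**The concern.** The article gives two study populations and one analysis rule, and the rule fits only one of them. If the 459 are analysed, the arms compared are not the arms that randomisation formed.

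The removals depend on the allocation itself. A person in the control group had no intervention to refuse, so nobody could leave that arm for the main reason given. The 5 illness removals are a further problem. They are reported in one arm only, and no withdrawal of consent is stated for them, so on the text shown intention-to-treat gives no ground for leaving them out.

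Both hypotheses of the trial rest on between-arm comparisons, and the senior meetings arm takes part in each. That arm loses about one person in seven.

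The same reduced set underlies the baseline comparison. The article places the baseline interview before randomisation, so baseline data were collected on all 491. Balance in a set trimmed after allocation cannot show that the allocation was sound.

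**Working it through.** **Inputs.** All counts come from the Procedure section. The outcome rates are assumptions, because the article states none.

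**1. Reproducing the article's figures**

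- Randomised: 114 + 178 + 199 = 491.
- Removed: 4 + 23 + 5 = 32.
- Left: 491 − 32 = 459; home visit 178 − 4 = 174; senior meetings 199 − 28 = 171; control 114 − 0 = 114.

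Every count agrees with the article.

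**2. Removal by arm**

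| Arm | Randomised | Removed | Share |
|---|---|---|---|
| Control | 114 | 0 | 0% |
| Home visit | 178 | 4 | 2.2% |
| Senior meetings | 199 | 28 (23 refused, 5 ill) | 14.1% |
| All | 491 | 32 | 6.5% |

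Senior meetings account for 28/32 = 87.5% of the removals. Fisher's exact test gives p = 0.000025 for senior meetings versus home visit and p = 0.0000018 for senior meetings versus control. Across the three arms, chi-square is 31.9 on 2 degrees of freedom (p about 0.0000001). Home visit versus control gives p = 0.16.

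**3. What removal can do to the contrast**

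Let the true deterioration rate be r in every arm (no treatment effect), and let the removed persons have rate q. With n randomised and m removed, the rate seen in those who remain is

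(n·r − m·q) / (n − m).

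Take r = 25%, so that n·r is 49.75 in senior meetings and 44.5 in home visit. Control stays at 25%.

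| q (assumed) | Senior meetings | Home visit | Spurious difference |
|---|---|---|---|
| 50% | (49.75 − 14)/171 = 20.9% | (44.5 − 2)/174 = 24.4% | 3.5 points in favour of senior meetings |
| 25% | 25% | 25% | none |
| 10% | (49.75 − 2.8)/171 = 27.5% | (44.5 − 0.4)/174 = 25.3% | 2.1 points against |
| 0% | 49.75/171 = 29.1% | 44.5/174 = 25.6% | 3.5 points against |

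Against control, the shift is 25 − 20.9 = 4.1 points in favour at q = 50%, and 29.1 − 25 = 4.1 points against at q = 0%.

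The power calculation aims at a 15% difference between the intervention groups. If that is read as percentage points, 3.5 points is 3.5/15 = 23% of it, in either direction.

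**4. Power is not the issue**

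The article requires 72 controls and 112 in each intervention group. The reduced arms of 114, 174 and 171 exceed this.

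**The case against.** **The article nowhere says that outcomes will be analysed on the 459.** This is true. The only analysis rule stated is by randomised group, the time plan speaks of 491, and the 459 appears in a description of participant flow and baseline. A reader might infer that the outcome analysis is already fixed on the 459, and the text does not establish that. What stands is the conflict: the 459 are presented as the study population, Table 2 uses them, and nothing shown keeps the 32 in. Detail on missing data may sit in a fuller document, but that does not reconcile two populations in this one.

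**Most of the loss was not an analyst's choice.** This is also true. Of the 32, 27 withdrew consent, and their follow-up data may simply not exist. Only 5 (5/199 = 2.5% of that arm) were taken out with no withdrawal stated. The 27 were nevertheless randomised, and an intention-to-treat analysis has to count them with their outcomes missing.

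**The tempting stronger reading is that the removals favour senior meetings, because the least motivated and sickest left that arm.** The documents do not support it. Four persons also left home visit. Nothing describes the health of those who refused, and the indirect evidence leans the other way. Of the 1120 who declined before randomisation, 936 had no interest, 116 lacked time and 68 lacked strength. The Discussion also says that participants did not see themselves as a target for aged-care interventions. If the refusers were healthier than average, removing them works against senior meetings.

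**A reader might also infer that dropping the 5 deletes primary-outcome events, since morbidity is a primary outcome.** That goes too far. Table 1 measures illness with CIRS-G at baseline, 1 year and 2 years, and the article gives neither the type nor the duration of these illnesses.

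**The criticism of the baseline tests is partly separate.** It would apply to the 491 as well. It belongs here because the inference is drawn from the reduced set.

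**Conclusion.** The point holds as an inconsistency that must be resolved. The article promises analysis by randomised group but describes a study population from which 32 of 491 (6.5%) were removed after allocation. Removal was strongly unequal: 0%, 2.2% and 14.1%. These counts are exact and need no assumption.

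Any comparison confined to the 459 loses the protection of randomisation. The size and sign of the resulting bias cannot be known from the article. Under the assumed 25% rate in every arm, the senior meetings versus home visit contrast moves by up to about 3.5 points either way as the rate among the removed goes from 0% to 50%. The 25% and the range of q are assumptions. The calculation also gives the removed in both arms the same rate.

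The Discussion's inference about randomisation does not follow from the 459.

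One discrepancy to correct alongside: Table 3 heads the control column n = 144, against 114 everywhere else.

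**What to change.** - Define the intention-to-treat set as all 491, in the arm drawn (114, 178, 199).
- Keep the 5 who fell ill in follow-up and in the analysis.
- Count the 27 who withdrew consent as randomised with missing outcomes, and use their pre-randomisation baseline data as far as consent allows.
- Add a sensitivity analysis for the missing outcomes in which the assumed risk among the removed runs both above and below that of the persons retained.
- Label any analysis of the 459 a modified set, and report removals by arm and reason beside it.
- Report baseline data for the 491 as consent allows, and delete the statement that non-significant differences show proper randomisation.
- Reconcile the time plan and the Procedure section on which number counts as included.

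The cost is some rewording and a little more analysis work. The estimate may become less favourable or less precise, but it will then answer the question that the stated principle commits the trial to.

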**Figure 1 F1:**
[figure not shown]
**Flow chart**. Flowchart throughout enrollment, allocation and baseline.

### Statistical analysis and power calculations

The calculations will be based on the expected relative change in time, i.e. we assume that the intervention group "Senior meetings and a follow-up home visit" will change slightly or not at all in functional status; that the intervention group "Preventive home visit" will change by 15% in relation to the intervention group with Senior meetings while the "Control group" will deteriorate 20% more than the intervention group "Preventive home visit". Power calculation ensures that, if the hypotheses are true, we will be able to discover a difference of at least 15% between the intervention groups and a difference of at least 20% between the intervention groups and the control group.

Since a level of significance of alpha = 0.05 and a power of 80% are required to compare the intervention groups in a two-sided test, at least 112 persons will be required in each intervention group to be able to observe a difference of at least 15% between the groups. A comparison between the control group and the intervention groups will require 72 persons in the control group, if we assume a difference of at least 20%. A total of about 300 persons will be required.

However, to allow for drop-outs, it was estimated that a total of about 450 persons would need to be included in the study.

The analyses will be made on the basis of the intention-to-treat principle, which means that the participants will be analysed on the basis of the group to which they have been randomised [34]. Both descriptive and analytical statistics will be used to compare the groups as well as for analyses measuring changes over time. Non-parametric statistics will be used in all cases where ordinal data are analysed. Otherwise parametric statistics will be used.

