#### Measurements of frailty indicators

##### Weakness

Grip strength was measured using a North Coast dynamometer [26]. The starting position was sitting on a chair comfortably. The shoulder should be adducted and neutrally rotated. The elbow should be flexed to 90 degrees. The forearm and wrist should be in a neutral position. The dynamometer was set to mode 2, as recommended in the manual. Measurements were carried out three times per hand, with a rest in between, starting with the dominant hand. The maximum value in the dominant hand was used. In this study, reduced strength was considered to be below 13 kg for women and 21 kg for males for the right hand, and below 10 kg for women and 18 kg for males for the left hand.

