##### Balance

This was measured with the Berg Balance Scale (BBS) [28,29] The instrument measures balance in 14 items and the assessment is made by observation. Every moment is scored using a 5-point scale (0-4). The instrument can be used on both individual and group level and has been tested for validity, reliability and sensitivity. The maximum score is 56 points. In this study, a value of 47 or lower was classified as a frailty indicator [30].

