##### Gait speed

Walking four metres at a comfortable speed was taken as a measure of gait speed. If the best speed value was 0.6 metres per second or slower, this was considered to be an indicator of frailty [31].

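### The protocol cuts measured primary scales at single thresholds, does not say whether indicator or scale is primary, and names no use of the collected baselines as covariates

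*Protocol article*

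**What the plan says.** **Primary outcomes.** The Primary Outcome Measures section lists frailty indicators, daily activities and morbidity. The measurement sections define most indicators by one cut on a measured scale. For Berg, scored 0-56, "a value of 47 or lower was classified as a frailty indicator". For gait speed, "If the best speed value was 0.6 metres per second or slower, this was considered to be an indicator of frailty". Walks are on a six-point scale and count as reduced at one to two per week or fewer. Fatigue and weight loss are single yes/no questions.

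**Grip.** The Weakness section says "The maximum value in the dominant hand was used". It then sets limits by right and left hand: 13 kg (women) and 21 kg (men) for the right, 10 kg and 18 kg for the left.

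**Baseline.** Every primary row of Table 1 is marked at T0. Entry requires an MMSE of at least 25 and independence in daily activities.

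**Analysis.** The section Statistical analysis and power calculations gives the rule "Non-parametric statistics will be used in all cases where ordinal data are analysed. Otherwise parametric statistics will be used". It also plans intention-to-treat group comparisons and analyses of change over time. It names no test, model or covariate.

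**Sample size.** The same section asks for "a level of significance of alpha = 0.05 and a power of 80% are required to compare the intervention groups in a two-sided test", and concludes that "at least 112 persons will be required in each intervention group" "to be able to observe a difference of at least 15% between the groups". The comparison with control "will require 72 persons in the control group, if we assume a difference of at least 20" per cent.

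**The concern.** Two choices that determine precision are left open or steered the less efficient way.

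First, a person who moves from 1.1 to 0.8 m/s does not change a gait indicator cut at 0.6 m/s. If the indicator carries the primary comparison, such changes do not count. If the scale carries it, they do. The article supports either reading, so the choice could be made after the data are seen.

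Second, the rule sends all ordinal data, hence Berg, walks and the ADL staircase, to non-parametric methods. The usual two-group rank tests do not take the baseline value as a covariate and treat persons as independent. Yet baseline values are available, and the Procedure section places people who live together in one arm.

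At stake is the width of the intervals obtained from the same participants, and the freedom to choose the form of the primary endpoint late.

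**Working it through.** **1. The plan's own sample size.** Stated inputs: two-sided alpha 0.05, power 80%, differences of 15% and 20%. No base rate or SD is given, so 112 and 72 cannot be reproduced from the stated inputs alone. Assume a 10% base rate, absolute differences and equal arms:

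n = [1.96·√(2p̄(1−p̄)) + 0.842·√(p₁(1−p₁) + p₂(1−p₂))]² / d², then the continuity correction (n/4)·[1 + √(1 + 4/(n·d))]².

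- 10% v 25%: 99.5, corrected 112.5 (113 rounded up). Stated: 112.
- 10% v 30%: 61.6, corrected 71.2 (72 rounded up). Stated: 72.

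A comparison of means does not fit both figures. The SD of about 40 that gives 112 for a difference of 15 gives 63 for a difference of 20 with equal arms, or 52 at a 112:72 allocation. The figures therefore look like a binary endpoint. That is an inference from an assumed base rate and not a statement in the article.

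**2. Information kept by a cut.** For a normal variable and a pure mean shift, a cut with proportion p positive keeps φ(z_p)²/[p(1−p)].

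| p | Information kept |
|---|---|
| 6% | 0.25 |
| 10% | 0.0308/0.0900 = 0.34 |
| 15% | 0.0544/0.1275 = 0.43 |
| 18% | 0.47 |
| 50% (best case) | 0.64 |

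Table 3 gives weakness 6-11%, gait speed 9-15% and poor balance 12-18%. The whole 6-18% range maps to about 25-47%. The upper end comes from Berg, where the normal model is doubtful. For grip and gait speed (6-15%) the range is 25-43%. These are baseline percentages; if more people are positive at follow-up, the loss is smaller.

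**3. Gain from baseline as covariate.** Let r be the baseline to follow-up correlation on the measured scale (assumed 0.3 to 0.7). Relative variances are 1 for follow-up only, 2(1−r) for change scores and 1−r² for the adjusted analysis. Adjustment thus saves r² against follow-up only, and 1 − (1−r²)/[2(1−r)] = (1−r)/2 against change scores.

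| r | Saving v follow-up only | Saving v change score | 112 becomes | 72 becomes |
|---|---|---|---|---|
| 0.3 | 9% | 35% | 102 | 66 |
| 0.5 | 25% | 25% | 84 | 54 |
| 0.7 | 49% | 15% | 58 | 37 |

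The last two columns are 112(1−r²) and 72(1−r²), rounded up. If 112 per arm gives 80% power for an unadjusted comparison of means, adjustment raises it to about 84%, 90% and 97.5%.

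**4. Where these gains do not apply.** Fatigue and weight loss are yes/no by design, so no cut loses information. Eligibility makes the binary baseline status for MMSE below 25 and for ADL dependence the same for everyone, so adjusting for it gains nothing. Berg is capped at 56 and MMSE is truncated at entry, so step 2 should not be applied to either.

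**5. Grip limits.** The value comes from the dominant hand, but the limit depends on right or left. A left-dominant person is therefore judged against a limit 3 kg lower than a right-dominant person of the same sex (13−10 for women, 21−18 for men). The share of left-dominant participants is not given.

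**The case against.** A reader might infer that the plan compares outcomes only by simple rank or parametric tests on dichotomised indicators, and so throws away most of the information and ignores baseline. The article does not say this.

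- The rule separates ordinal from other data, which suggests that at least some scales are analysed as scales. Table 1 lists the instruments themselves as outcome measurements. The cut-offs define when an indicator is positive; they do not say that the measured value is dropped.
- Change over time is to be analysed, so baseline values are used in some way. Parametric methods can include covariance and mixed models.
- Rank tests can be run on change from baseline, can be stratified and can come with effect estimates. For normal data they keep about 95% of the efficiency (3/π), so the rank rule alone is not costly.
- Thresholds answer the stated question of whether frailty can be prevented. Demoting them would change the question and not correct an error.
- Full model specification and the handling of death commonly sit in an analysis plan, which is not shown.

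All of this stands, and it limits the point. It does not settle which form is primary, and it does not supply a use of baseline as covariate. Against change scores, the approach nearest to what the article describes, adjustment still saves 15-35% over the assumed range of r. The grip mismatch is also untouched.

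**Conclusion.** The point holds as a recommendation to fix the form of the primary comparison and to use baseline values as covariates. It does not show that the planned analysis is invalid.

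Its size depends on what is done. If the indicator alone is used for a roughly normal measure such as grip or gait speed, about 34-43% of the information on a mean shift remains at 10-15% positive. That rests on normality, a pure shift and baseline prevalence. The gain from baseline adjustment is 9-49% of the variance against follow-up only and 35-15% against change scores, for r from 0.3 to 0.7; r is assumed throughout.

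The documents do not support the inference that most decline or benefit goes unseen. The 6-18% positive is measured at baseline, while outcomes run to two years in people with a median age of 85-86. The grip definition is a real inconsistency, but probably a small one in effect.

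**What to change.** 1. State for each primary frailty measure whether the threshold indicator or the measured scale carries the primary comparison.
2. Keep the threshold indicators for the question of preventing frailty, and adjust each for the measured baseline value where one exists.
3. Also analyse grip (kg) and gait speed (m/s) on the measured scale with the baseline value as covariate.
4. Replace the blanket non-parametric rule with a baseline-adjusted ordinal model for Berg, walks and ADL where the baseline value varies.
5. Allow for households placed in the same arm.
6. Reconcile the Weakness section so that the dominant-hand value and the right- and left-hand limits agree.

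The cost is revised wording, a little more modelling and a proportional-odds assumption to check. No new data are needed.
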